### 3.3.2 Study flow diagram

The diagram shows the intervention of social media listening (SML) and clinical trial recruitment via Twitter (see page 11).

### 3.3.3 Eligibility: Trial and participant selection

#### *TRIAL*

General characteristics of clinical trials to be enrolled: Eligible trials will focus on one the six pre-selected cancer disease types, i.e., non-small cell lung cancer, colon cancer, breast cancer, prostate cancer, kidney cancer, lymphoma. This trial selection is independent of stage of disease. The disease categories we selected are based on a preliminary Twitter user data analysis in California (Table 1, **Appendix 1**) and the number of prospective, recruiting trials at USC Norris (**Appendix 2**).

Eligible clinical trials must:

- focus on one of the following disease categories: non-small cell lung cancer, colon cancer, breast cancer, prostate cancer, kidney cancer, lymphoma,
- be a Phase 1 trial in expansion, Phase 2, or 3,
- be interventional trials,
- recruit in English,
- be IRB-approved and open to accrual at USC Norris,
- recruit for at least 9 months at the point of enrollment, and
- set monthly accrual target  $\geq 1$ / and annual accrual target  $\geq 12$ .

Exclusion criteria: Phase 1 trials in dose escalation.

**Table 1.** Total social media activity on Twitter among English-speaking populations from January 1, 2016 to January 30, 2017 in California for pre-select cancer disease terms. See

**Appendix 1** for detailed analysis of Twitter user activity by cancer type. *Note: The preliminary Twitter user activity data were provided by our private-sector partner Symplur for free. At the onset of this project, we will have access to the Symplur Signals database and will be able to refine the search focused on Twitter user for LA County.*

| Location                                                                                                          | California |
|-------------------------------------------------------------------------------------------------------------------|------------|
| Total number of Twitter messages (in English) that include pre-selected disease terms                             | 159,396    |
| Total number of Twitter users who used pre-selected cancer disease terms in one or more of their Twitter messages | 36,502     |

**Anticipated number of clinical trials:** Based on a preliminary data analysis (**Appendix 2**), at this point in time there are 84 clinical trials open at USC Norris that meet the criteria for inclusion in this study. SML will be used to identify potential participants for all these trials.

[figure not shown]

**Figure 1. Study flow diagram of study design, procedures and stages for intervention A.**

## PARTICIPANTS

General characteristics of the proposed participant population(s): Any Twitter user who mentions one or more of the pre-selected cancer disease topics will be contacted via Twitter.

Anticipated number of research participants: We anticipate increasing the number of participants enrolled per trial and per month based on the following historic data from the past five years (see **Appendix 2**):

- Non-small cell lung cancer: Minimum of 2 participants per month
- Colon cancer: Minimum of 2 participants per month
- Prostate cancer: Minimum of 3 participants per month
- Breast cancer: Minimum of 2 participants per month
- Kidney cancer: Minimum of 1 participants per month
- Lymphoma: Minimum of 1 participants per month

Inclusion criteria for prospective trial participants: We will include all prospective trial participants in this study that come from Twitter in response of our SM recruitment interventions, provided they meet the specific trial's eligibility criteria.

Exclusion criteria for prospective trial participants: Persons who do not meet the eligibility criteria of any of the trials open to accrual will be excluded from participation, and persons who may be eligible (e.g., disease/histology, stage, prior treatment) but do not meet additional trial-specific requirements such as insurance or allergy to drug). These may vary by clinical trial. We will count these people as engaged but not enrolled and document the specific reasons.

Screening procedures: We will use the eligibility criteria as outlined above to verify clinical eligibility for participation in the study.

### *3.3.4 Study intervention*

We will use Symplur Signals, a healthcare SM analytics platform that maintains a database of curated disease- and health-related Twitter conversations and user data, updated daily and easily sortable by SM user type (patient, physician, health care organization), location and time zone, language, disease/health interests, message content, sentiment, and SM influence.

We will use prospective data as well as retrospective data (last 6 months at the time of project implementation) to identify users on Twitter in LA County who mention specific cancer disease keywords and/or hashtags and contact them to recruit them into clinical trials. A hashtag is a word or phrase preceded by a hash or pound sign (#) that is used to identify messages on a specific topic on Twitter (e.g., #diabetes, #stroke). Table 2 lists a limited overview of the keywords or hashtags we will use for monitoring during the project period. The full list of keywords and hashtags relevant to the six cancer disease terms will be extracted from the Symplur database at the onset of the project because part of the information is proprietary and only accessible after purchasing data access.

Those individuals are then targeted for recruitment using a combination of SM and traditional methods. We aim to recruit all trials (84) open for recruitment to accrual for treatment of patients with non-small cell lung cancer, prostate cancer, breast cancer, colon cancer, kidney cancer, or lymphoma at USC Norris. Disease categories will be randomized and rolled in consecutively, one every two weeks in the first quarter. Each trial will be exposed to the intervention for 9 months.

**Table 2.** Limited list of keywords or hashtags that will be used for monitoring Twitter user conversations in LA County during the project period. (Reference: <https://www.symplur.com/>)

| Cancer disease type        | Keywords and hashtags to be monitored                                                         |
|----------------------------|-----------------------------------------------------------------------------------------------|
| Breast cancer              | #breastcancer
#BCSM (breast cancer and social media)
breast [AND] cancer                |
| Colon cancer               | #CCSM
#ColonCancer
#ColorectalCancer
colon [AND] cancer
colorectal [AND] cancer   |
| Kidney cancer              | #KidneyCancer
kidney [AND] cancer                                                          |
| Lymphoma                   | #Lymphoma                                                                                     |
| Non-small cell lung cancer | #LCSM (lung cancer and social media)
#LungCancer
lung [AND] cancer [AND] non-small cell |
| Prostate cancer            | #PCSM (prostate cancer and social media)
#ProstateCancer
prostate [AND] cancer          |

We will send identified Twitter users IRB-approved messages via the Twitter account we create for the purpose of this project @USCNorrisTrials to attract their attention, engage, and recruit them into the enrolled clinical trials. Message example: @JaneDoeA, this may be of interest to you. Researchers @USC are looking for participants for this new #LungCancer trial [Link to clinical trial webpage]. See **Appendix 3** for overview of Twitter outreach message templates.

Outgoing messages will be public and organic (not advertised). Twitter does not permit paid advertisement for clinical trials. The messages will refer recipients to the respective cancer disease trial group webpage hosted by the USC Clinical Studies Directory. For example, a message may promote lung cancer trials at USC Norris and refer Twitter users to the webpage that lists all recruiting lung cancer trials at USC Norris. An easy-to-use contact form that asks for the name and email can be used by the user to contact the study team. See **Appendix 4** shows an example of such a webpage. The web page content used for this research will be submitted to the IRB once we enroll the trials and know their focus and consent information. The consent information will guide the content we use on the web pages.

Using the contact form on the web page will trigger an email to the SC CTSI study team ([name], [name]) who will then triage the request to the respective cancer disease contact at USC Norris. See also Figure 1. For the purpose of tracking, we will tag each message through an element descriptor in the Hypertext Markup Language. This will allow us to determine the recruitment results by individual and message.

There is no active control group in this study. Success will be compared to historical success achieved without the use of SML at USC Norris for trials in the selected disease cancer categories.

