| Primary outcomes                                      | 1. Feasibility : Acceptance of and satisfaction with SM recruitment method among USC Norris study team members and Twitter users in LA County, number of cancer trials eligible to be enrolled in study, number of cancer disease types and studies that can be monitored for on Twitter simultaneously by the SC CTSI study team, time and effort it takes the SC CTSI and USC Norris team members to respond to the resulting inquiries and decide whether or not to bring the patient in for screening, eligibility rate of prospective participants, demographic and ethnic diversity rate of those who consented/enrolled, social media message click rate, website contact form usage rate.
2. Impact : Monthly observed recruitment rate vs. monthly projected accrual target by trial disease group compared to historic data. Effect size estimate of the number of people to enroll cancer trials as a result of targeted social media listening and recruitment (SML) via Twitter.                                                                                                                                                                                                                                                                                                                                                                                                                                                                                                                                                                                            |

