## 1.4 Anticipated duration of the clinical investigation

We estimate 14 months to complete the proposed study including the data analysis and dissemination. The intervention exposure time is 9 months per enrolled trial. Disease categories will be rolled consecutively, one every two weeks in the first quarter. Order will be randomized.

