### 3.3 Study design

#### 3.3.1 General study design

We will use a mixed-methods interrupted time series study design with a before and after intervention at the USC Norris Comprehensive Cancer Center (USC Norris). This study will examine the feasibility and gain preliminary data on the impact of targeted social media listening (SML) as a tool for enhancing recruitment to cancer trials (non-small cell lung cancer, colon cancer, breast cancer, prostate cancer, kidney cancer, lymphoma) among Twitter users in LA County. Disease categories will be randomized and rolled in consecutively, one every two weeks in the first quarter. The order will be randomized.

We aim to recruit all interventional trials in the select disease areas (84; based on USC Norris data from 1/1/2017 to 07/07/2017) open for recruitment to accrual for treatment of patients with non-small cell lung cancer, prostate cancer, breast cancer, colon cancer, kidney cancer, or lymphoma) at USC Norris. We may include another tumor type if the number of trials is insufficient or other tumor types and Twitter user activity emerge that are of interest to the research question. Disease categories will be randomized and rolled in consecutively, one every two weeks in the first quarter. Once a study is enrolled it stays on for the period of this study. Each trial will be exposed to the intervention for 9 months. This design was chosen to fit within the triage protocol of USC Norris and cause minimal disruption to the staff. Success will be compared to historical success achieved without the use of SML.

Outcomes will be the feasibility of the study described by the acceptance of and satisfaction with SM recruitment method among USC Norris study team members and Twitter users in LA County and by describing the proportion of eligible cancer trials to be enrolled in the study, cancer disease types and studies that can be monitored at a time, eligible participants that can be enrolled, diversity of participants, staffing required to monitor eligible studies, burden of recruitment/cost of intervention.

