The **efficacy** aim will be determined comparing monthly actual vs. projected rate of recruitment for the trial disease groups (i.e., non-small cell lung cancer, colon cancer, breast cancer, prostate cancer, kidney cancer, lymphoma) and compared to historic data by trial disease group using generalized estimating equations, accounting for intra-disease random effects and trends across the 12 months (9 months exposure per trial). Statistical analyses of primary aims will be carried out by [name] [name], an SC CTSI biostatistician. Analyses will be performed in SPSS v24 [41]. As this is a pilot study, p-values are of limited use to determine group differences, so we will focus on observed effect sizes (Cohen's D, Relative Risk).

**Table 3** lists all primary outcomes measures we intend to use. In addition, **Appendix 5 (data dictionary)** provides the full set of metrics we will use to assess the success of the intervention, which includes additional success metrics such as number of contacts solicited, number of contacts who acknowledge the solicitation, number of social media contact/recruitment messages sent, day/time of contact, day/time of response.

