| Website contact form usage rate      | Number of times a contact form was used on a trial webpage/Number of webpage sessions ( Sessions: Group of interactions a user takes on a webpage or website within a given time frame, e.g., page views, clicks. )                                                                                                                                                                                                                                                                                     |
| User acceptance and satisfaction (%) | 
 
• Number of USC Norris study team members who are satisfied with the SM monitoring and recruitment intervention/Number of all study team members engaged
 
• Number of PIs that are willing to participate (acceptance by PIs)
 
• Number of trial participants enrolled (Twitter users in LA County) who are satisfied with the SM monitoring and recruitment intervention/Number of all people engaged (i.e., who spoke with the study team)
 
 |
| IMPACT AND EFFICACY           |                                                                                                                                                                                                                                                                                                                                                                                                                                                                                                                |
| Enrolment rate per month             | 
 
• Number of people enrolled per month/Number of people contacted on Twitter per trial per month
 
• Number of people triaged and enrolled in another trial per month/Number of people contacted on Twitter per trial per month
 
                                                                                                                                                                                                                        |

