## APPENDIX 3: Overview of Twitter Outreach Message Templates

### Twitter recruitment message templates we propose to use for contacting those Twitter users in LA County

*(i.e., those who mentioned one of the select disease categories lung cancer, colon cancer, breast cancer, prostate cancer, kidney cancer and lymphoma in the past 6 months or during the research study period)*

*Abbreviation: URL = Uniform Resource Identifier is the global address of documents and other resources on the World Wide Web. The URL to the respective trial group will be included in each Twitter recruitment message. For example, a message about open lung cancer trials at USC Norris will link to the web page that lists all lung cancer trials.*

*#disease will be replaced by the respective disease.*

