#### FOLLOW-UP IF NO RESPONSE AFTER INITIAL CONTACT

*If a prospective participant does not respond, we will send a one-time follow-up message within two weeks of initial contacting.*

Dear @JaneDoe or Hi @JaneDoe,

- Let us know if you have any questions about open #disease trials @KeckMedUSC. We'd be happy to help. Feel free to send us a direct message.

- We're following up on our previous message about clinical trials @KeckMedUSC. Feel free to contact us via DM if you have any questions. We'd be happy to help.
- Let us know via direct message if you have any questions about #disease trials @KeckMedUSC. We'd be happy to help.
- Did you have any questions about ongoing #disease trials @KeckMedUSC? Let us know. Feel free to contact us via DM. We'd be happy to help.

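### Table 3 divides a month's enrolments by the same month's Twitter contacts, and the six-month retrospective pool is not kept apart from prospective contacts

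*Protocol*

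**What the plan says.** Section 3.3.4 draws the people to be contacted from two sources: prospective data and "retrospective data (last 6 months at the time of project implementation". Appendix 3 repeats this, addressing users who mentioned a selected disease "in the past 6 months or during the research study period". Neither place says when, or how fast, the retrospective group is messaged.

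Under Impact and Efficacy, Table 3 gives two enrolment lines. The first is "Number of people enrolled per month/Number of people contacted on Twitter per trial per month". The second counts people triaged into another trial and uses the same denominator.

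The Synopsis states impact differently: "Monthly observed recruitment rate vs. monthly projected accrual target by trial disease group compared to historic data". Section 3.3.7 analyses that comparison with generalized estimating equations that allow for "trends across the 12 months (9 months exposure per trial".

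On timing, Section 3.3.1 says "Each trial will be exposed to the intervention for 9 months", and Section 1.4 brings disease categories in "one every two weeks in the first quarter". For people who do not respond, Appendix 3 says "we will send a one-time follow-up message within two weeks of initial contacting". After a response come the contact form, triage by the study team and eligibility screening by the cancer center team (Section 3.3.4, Table 4).

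**The concern.** A rate per contact is readable only if the enrolments counted came from the contacts counted. The Table 3 ratio pairs them by calendar month instead. Someone messaged late in one month who passes through the form, triage and screening may well enrol in a later month, and is then divided by that later month's contacts.

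With steady contact volume this would be little more than a start-up effect. The retrospective pool is a finite stock added to the flow of new users, so volume may not be steady. Nothing in the protocol separates the two sources in the outcome. A one-time stock cannot be drawn on again each month, and older mentions may yield differently from fresh ones.

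Table 4 says the pilot's preliminary data will support a larger grant proposal. If the monthly ratio, or a yield that mixes the two sources, is carried forward as what the method delivers each month, later planning rests on the wrong number.

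**Working it through.** The protocol states no expected enrolment rate, lag or contact volume, so there is no figure of its own to reproduce. The following is an illustration for one disease group.

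**Inputs from the protocol:** a six-month look-back (Section 3.3.4), nine months of exposure (Section 3.3.1) and the same-month ratio (Table 3).

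**Assumptions:**
- New contacts run at 1 unit per month and the true yield per contact is 1.0.
- The retrospective pool is B units, with B = 2, 3 or 6. B = 6 means users arrive evenly without repeats; the lower values allow for repeat posters.
- The pool is messaged in month 1, evenly over months 1 to 3, or evenly over all nine months.
- Enrolment comes after 0, 1 or 2 months, or is spread over months 0 to 3 as 10/40/30/20%.
- A retrospective contact yields as much as a new one, unless stated.

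**Formula.** With C(m) the contacts in month m and w(k) the share enrolling k months later, enrolments are E(m) = Σ w(k)·C(m−k), and the Table 3 rate is E(m)/C(m).

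**B = 6, messaged in month 1.** C(1) = 7, every later month is 1, and the total is 15. Month 1 holds 7/15 = 47% of contacts.
- Lag of 1 month: month 1 = 0/7 = 0; month 2 = 7/1 = 7.0; then 1.0.
- Lag of 2 months: 0, 0, 7.0, then 1.0.
- Spread lag: month 1 = 0.7/7 = 0.1; month 2 = 0.1 + 0.4×7 = 2.9; month 3 = 0.1 + 0.4 + 0.3×7 = 2.6; month 4 = 0.1 + 0.4 + 0.3 + 0.2×7 = 2.2; then 1.0.

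**Peak single-month rate by scenario (equal yield):**

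| Pool B | Messaged | Lag 1 month | Spread lag |
|---|---|---|---|
| 6 | month 1 | 7.0 | 2.9 |
| 6 | months 1–3 | 3.0 | 2.8 |
| 3 | month 1 | 4.0 | 1.7 |
| 3 | months 1–3 | 2.0 | 1.9 |
| 2 | month 1 | 3.0 | 1.4 |
| 2 | months 1–3 | 1.67 | 1.6 |

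Month 1 reads 0 with the one-month lag and 0.1 with the spread lag in every row. A two-month lag gives the same peaks as a one-month lag.

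**Where the spike disappears:**
- No lag and equal yield: 1.0 in every month.
- Pool spread over nine months, spread lag: 0.1, 0.5, 0.8, then 1.0. This is the same start-up pattern as with no pool at all.

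**Mixing without any lag.** If a retrospective contact yields half as much, B = 6 in month 1 gives (1 + 0.5×6)/7 = 0.57 in that month. Spread over nine months, every month reads (1 + 0.5×0.667)/1.667 = 0.80, although new contacts yield 1.0.

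**Pooled ratio (B = 6, month 1, equal yield).** Total enrolled over total contacted is 14/15 = 0.93 (lag 1), 13/15 = 0.87 (lag 2) or 13.4/15 = 0.89 (spread). The shortfall from 1.0 comes from people contacted too late to enrol by month 9. The median monthly rate is 1.0 in all three.

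**Enrolment counts.** With B = 6 and equal yield, enrolments arising from Twitter average 15/9 = 1.67 (no lag), 14/9 = 1.56 (lag 1), 13/9 = 1.44 (lag 2) or 13.4/9 = 1.49 (spread) times the steady monthly number. This holds whether the pool is messaged in month 1 or over three months. With B = 2 and lag 1 it is 10/9 = 1.11.

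**The case against.** The strongest objection is that the protocol never says the pool is messaged at the outset. It gives a look-back window for finding users, and how much the team can handle is itself a feasibility question. A reader might infer that seven months' worth of contacts land in month 1, that month 1 must read close to zero, and that later enrolments are counted at seven times their weight. The documents do not support this as fact. It needs front-loading, even arrival and one fixed lag, and none of these is stated. It is the top of the range.

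A reader might also infer that the per-contact yield is inflated overall. It is not: the pooled ratio in the worked cases is 0.87 to 0.93 of the true value, and the median month is right.

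Nor does the mismatch feed the Section 3.3.7 model as a false trend. That model compares actual with projected accrual and has no contact denominator. Only the extra enrolments from the pool can reach it, as a contribution that does not recur. The documents do not give the share of accrual that comes from Twitter, so the effect on total accrual cannot be sized.

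It is fair, too, that the ratio is not the only impact measure, although it is the only one under that heading in Table 3. A pilot may also legitimately measure the intervention as delivered, look-back included.

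Two things stand after all this. The ratio is a formula fixed in the protocol, not a detail left to an analysis plan, and it pairs enrolments with contacts they need not have come from. And no stated outcome separates the one-time pool from the continuing flow.

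**Conclusion.** The point holds as a defect in a stated definition, worth correcting but limited in reach. Numerator and denominator can be different people whenever enrolment falls in a later month than contact. The steps between the two make that likely, though no length is given.

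If the pool is messaged early, single-month rates could run from about 0 to a peak of 2.8 to 7 with a sixfold pool, or 1.4 to 4 with a two- or threefold pool, against a true 1.0. These figures rest on the assumed lag, pool size, schedule and equal yield. They vanish with no lag and equal yield, or when the pool is spread over nine months. Even then, unequal yield between the sources would stay hidden in the combined ratio.

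The accrual model is untouched by the ratio, but its counts may include a non-recurring part.

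**What to change.** Redefine both Table 3 enrolment lines by contact cohort: of the people first contacted in period t, the number enrolled by study end, with follow-up time stated for each cohort. In the illustration this returns each source's own yield for every cohort with adequate follow-up, whatever the lag or pool size.

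Derive retrospective or prospective status from the date of the user's own tweet and the implementation date. Report the two sources separately as well as combined, and use the prospective yield for ongoing monthly yield. State how to class tweets posted between implementation and a disease's own start, since with six diseases the last begins about 5 × 2 = 10 weeks after the first. When reading actual against projected accrual, show how many enrolments came from the retrospective pool.

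The data cost is small. Appendix 5 already lists the tweet date, the contact date and a yes/no enrolment field, and Section 3.3.4 plans tracking by individual and message. Appendix 5 lists no enrolment date. The present monthly numerator needs one, while the cohort count by study end does not. The real cost is that late cohorts have less time to enrol, so their yields must be shown with their follow-up and not read as a decline.
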